## Abstract

**Background:**

Mindfulness-based interventions, modified and shortened versions of meditation teachings, have proved to be effective in the improvement of quality of life in many clinical conditions, including chronic diseases. Preliminary results available in the literature and in clinical experience indicate a high potential for this treatment for the reduction of psychological suffering in people with chronic diseases.

**Methods/Design:**

This randomized controlled trial will investigate the impact of a multiple sclerosis (MS) specific telemedicine meditation intervention on the quality of life of people with multiple sclerosis and their caregivers. This trial will recruit 120 patients, men and women, with a diagnosis of relapsing-remitting or secondary progressive MS and their caregivers to participate in a 2-month intervention. Patients will undergo assessments of quality of life, anxiety, depression, quality of sleep, mindfulness and fatigue levels conducted at baseline, at week 8 (conclusion of the intervention) and at week 27 (6 months follow-up). Caregivers will complete assessments conducted at the same time for the same areas, plus caregiver burden. The intervention condition will consist of 2 hours/week of online meditation in a group setting led by a trainer, plus 1 hour/week of individual exercises. The control condition will incorporate a psycho-education online program and will require the same contact time commitment as the intervention condition.

**Discussion:**

Primary outcome measures will consist of assessments of quality of life, anxiety, and depression level. Assessments of mindfulness level, quality of sleep and fatigue level will be considered secondary outcome measures.

This investigation will increase understanding of the role of meditation as part of a treatment plan for people with MS and their caregivers. Overall, this study design has the potential to lead to effective meditation intervention strategies for this population and improve their quality of life.

**Trial registration:**

Clinical Trials Register NCT02364505. https://clinicaltrials.gov/ct2/show/NCT02364505

## Background

Multiple sclerosis (MS) is a chronic disease of the central nervous system that results in worse quality of life than that experience by persons living with other chronic diseases [1]. The unpredictable and variable nature of MS makes it particularly difficult to accept; moreover, the grim prognosis and the added unpredictability of day-to-day health in relapse-remitting MS and side effects of medication [2] greatly impact quality of life and quality of sleep. Fatigue, anxiety, and depressive features are often reported by people who have MS [3–5]. In particular, lifetime prevalence of major depressive disorder is approximately 50 % [6]. Moreover, the impact of care for this kind of disease on family caregivers can be very high: caregivers often suffer from sleeplessness, fatigue, anxiety, depression, and impaired immunological responses [7].

Psychological interventions may be effective in the reduction of distress, anxiety, and depression, also reducing MS symptoms [8], but further exploration is required. Meditation teachings have proved effective in the improvement of quality of life in many clinical conditions [9–11], including chronic diseases [12, 13], although accessing it is a challenge for a part of the population [14, 15]. In a previous study, the use of a standard meditation protocol was found to promote an improvement in psychological well-being of people with MS [16]. Patients with MS who were assigned to meditation condition experience an improved quality of life, and reduced levels of fatigue and depression up to 6 months after the intervention. Study limits included the fact that the protocol was designed for the general population, not for the clinical peculiarities experienced by people with MS. Moreover, the clinical needs and problems of these people might prevent full participation in meetings. Lastly, MS caregivers may benefit from this treatment, but neither this study, nor any other study, has yet explored this option in depth.

Available data suggest a relevant clinical potential for an online meditation treatment for people with MS and their caregivers. While treatments provided through technological platforms (telemedicine in particular) have been developed for other populations in recent years [17], few MS-related programs take advantage of the internet and related telecommunication platforms. Some promising efforts have begun: results from a recent pilot study [18] suggested that a problem-solving 5-week internet-based self-help program benefited MS patients with depressive symptoms.

### Aims

The main study aims are as follows:To create and test a multimedia software that can teach meditation at home, following the specific requirements of people with MS.To investigate the effects of this telemedicine mindfulness training on the improvement of quality of life of MS caregivers. While protocol changes will be made according to MS peculiarities, the resulting protocol will also be suitable for healthy populations, including MS caregivers.To assess whether patients undergoing this meditation protocol show a change in their sleep patterns, which may reflect an improvement in their quality of life.

## Methods/design

### Study design

The study design of the randomized controlled trial is composed of two arms (experimental and control groups, both of 8 weeks duration) and three assessments (2 × 3 design): baseline, directly after treatment, and 6-months follow-up. Each participant will provide informed consent. Ethical committees from both the Catholic University of Milan (reference 19-12-2013) and the Fondazione Don Gnocchi (reference FDG_9.4.14) have approved the project. Results will be published in both scientific and general-audience media.

### Meditation and control protocols and software development

The first part of the project is dedicated to the adaptation of the meditation protocol to MS requirements and clinical peculiarities, the creation of the software, and a testing phase. To maximize its effectiveness [19], the meditation protocol will consider the potential impact of MS symptoms (e.g., numbness, fatigue, tingling), implementing meaningful changes to be more MS-related than the original mindfulness-based stress reduction protocol, for example, by implementing music meditation experiences and relaxation exercises. The protocol will be implemented using multimedia software, which will provide the learning and the practice of the intervention. It will be a course, provided with audio and video stimulations, with multiple interactions with the trainer. At the same time, an online control intervention will be implemented. This control intervention includes a psycho-education online program about MS, characterized by interviews, practical advice, and exercises [20]. The contact time commitment will be the same for both conditions.

### Software testing

After the development of the software, it will be tested for ergonomics and usability. Five patient–caregiver couples will receive the software and be instructed in its use. Their qualitative feedback, during the 2 months of the intervention and afterwards, will be useful in making changes that could improve the usability and reduce unexpected events (e.g., code program errors).

### Sample size and recruitment

We aim to recruit 120 people with MS together with their primary caregivers (therefore, the potential sample is up to 240 subjects; 120 patients and 120 caregivers).

Inclusion criteria for patients with MS will be:Diagnosis of relapsing-remitting or secondary progressive MS (divided into 60 relapsing-remitting and 60 secondary progressive during the recruitment procedure);Ability to communicate and to understand tasks;No change of disease-modifying treatment in the 3 months before the enrolment;No clinical relapses or use of steroid treatment during the 4 weeks before the enrolment;Availability of a personal computer, smartphone, or tablet (compatible with the software);Provided informed consent for study participation;Age >18 years.

Inclusion criteria for caregivers will be:Being a person who lives with the MS patient and provides him or her with the most care and assistance;Ability to communicate and to understand tasks;Availability of a personal computer, smartphone, or tablet (compatible with the software);Provided informed consent for study participation;Age >18 years.

Exclusion criteria (referred to both patients and caregivers) will be:Severe co-morbidity that would reduce life expectancy to less than one year (e.g., end-stage oncological diseases or severe cardiac dysfunction);Severe neuropsychological impairment (e.g., dementia), as indicated by testing below the fifth percentile in at least 3 of 6 dimensions of neuropsychological functioning tests (i.e., attention and concentration, processing speed, executive function, verbal memory, and verbal processing);Psychosis or dissociative disorders;Pregnancy.

Subjects will be recruited at the Multiple Sclerosis Center of the Fondazione Don Gnocchi Hospital, in Milan.

### Procedure

Progression to the study is outlined in Fig. 1.

**Fig. 1 Fig1:**
[figure not shown]
Overview of study procedure

### Screening, assessments, and randomization

Screening will be conducted by doctors of the Multiple Sclerosis Center of the Fondazione Don Gnocchi Hospital, considering the inclusion and exclusion criteria.

Subsequently all subjects will be fully assessed at baseline (T1), after 2 months (T2, corresponding to the end of treatment) and at 6-months follow-up (T3).

Primary outcome measures will assess quality of life, together with depression and anxiety. Attained mindfulness level, quality of sleep, and participation level will be considered secondary outcome measures. Questionnaires will be self-reported, with online assessments (therefore accessible from subjects’ own computers). Subjects will be also assessed, with a qualitative approach (semi-structured interview), about possible side effects or adverse events of the treatment, at T2 and T3, by a psychologist. The interview will be conducted in person or via teleconference call (e.g., Skype).

Subsequently, randomization will be conducted by the principal investigator who will be fully blinded to all patient information, except the study identification numbers of patients. Patient–caregiver couples will be considered as single units for the randomization.

Subjects, consisting of patient–caregiver couples, will be randomly allocated into two groups (60 patients + their caregivers for each groups, with a stratification referred to subjects recruited for the instrumental assessment):Meditation telemedicine intervention, developed and tested.Control group, receiving psycho-education, utilizing a telemedicine approach.

The intervention phase will begin at the end of the pilot study (month 6) and will last 11 months.

In the mainframe of the general study, an objective evaluation of the impact of treatment on sleep disturbance and fatigue will be conducted with an instrumental assessment. During the software development and testing phases, we will consecutively recruit 40 subjects with MS (first recruitment round), with the same inclusion criteria, who report disturbed sleep. Each of these subjects will undergo actigraphy. The sensor will be worn by each subject for two consecutive weeks and will provide objective information about quality of sleep and daily activity, with synthetic data summarized by a computer software.

As soon as the intervention phase begins, these 40 subjects will be randomly allocated to one of the two groups and will undergo all the psychometric assessments, as for the other participants. These subjects will be assessed by actigraphy again, in a post-intervention assessment. The method will remain the same, with an identical timeframe (2 consecutive weeks).

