### Analysis

The general linear model will be used to test interaction effects between treatments (experimental versus control groups) and over time (three repeated measures). Six models will be built, one of each primary outcome measure (quality of life, anxiety, and depression) and separately for patients and caregivers. Type I error inflation due to multiplicity of tests will be controlled by the correction of critical alpha (0.05/6 = 0.008). Violations of the parametric model assumptions will be tested and explored with ad-hoc techniques. If violations are detected, robust methods, data manipulation, or statistical corrections will be applied accordingly. An intention-to-treat analysis approach will be used. Missing data will be imputed with multiple imputation techniques [28]. According to power analysis calculation (G*Power), a total sample size of 110 patients (and caregivers) will allow the detection of small interaction effects (*η*^2^ = 0.01) with a 0.85 statistical power, alpha = 0.05 and an assumed nonsphericity correction (*ε*) of 0.75. Significant interaction effects will be followed by contrast analysis. A similar analysis will be conducted for the actigraphic data, with a reduced sample size, enabling the detection of a small-medium interaction effect under the same conditions.

The mediation effect of the meditation level will be examined by adding a within-subjects factor to the general linear models and the interactions with the treatment effect will be explored according to the guidelines of Kraemer *et al.* [29]. In addition, moderation effects by sex, age, and number of accesses to the software will be examined by adding the relative between-subjects factors into the general linear models and the interactions with the treatment effect will be explored according to the same guidelines [29].

Data analysis will be performed with R and SPSS software.

Data collection and analysis will begin at month 1, and will last 21 months, 1 month after the last follow-up data gathered.

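### The first actigraphy of the 40 sleep-disturbed patients is placed in the software phase, up to 5–6 months before randomisation; recording it next to T1 would be a cheap improvement

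*Protocol article*

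**What the plan says.** All places are in the protocol article.

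- **Recruitment of the subset** (Screening, assessments, and randomization): "During the software development and testing phases, we will consecutively recruit 40 subjects with MS (first recruitment round), with the same inclusion criteria, who report" […]. The patients are chosen because they report disturbed sleep.
- **First recording** (same section): "Each of these subjects will undergo actigraphy", and "The sensor will be worn by each subject for two consecutive weeks". No calendar date is given. The order of the text places the recording after this early recruitment and before allocation.
- **Allocation** (same section): "As soon as the intervention phase begins, these 40 subjects will be randomly allocated to one of the two groups". The intervention phase starts at month 6. The psychological baseline also starts at month 6 (Measures), whereas data collection starts at month 1 (Analysis).
- **Second recording**: after the intervention, with the same two-week format. No other recording is described.
- **Objective** (Aims): "To assess whether patients undergoing this meditation protocol show a change in their sleep patterns".
- **Analysis**: a treatment-by-time model similar to the main one, on the reduced sample, "enabling the detection of a small-medium interaction effect under the same conditions".
- **Stability criterion** (Sample size and recruitment): "No clinical relapses or use of steroid treatment during the 4 weeks before the enrolment". A 3-month window for changes of disease-modifying treatment is likewise counted back from enrolment.

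**The concern.** A baseline for an 8-week treatment is most useful when taken just before the treatment starts. Here it is taken while the software is still being built, and the delay differs from patient to patient. Three things follow.

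1. The change between the two recordings covers the wait as well as the treatment. In patients selected for reporting bad sleep, in a disease that the Background describes as unpredictable and variable, the wait may bring its own drift.
2. A more distant baseline usually correlates less with the outcome. That costs precision, and the comparison has only about 20 patients per arm.
3. Objective and self-reported sleep are measured at different times before treatment, so their changes cover different periods.

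Also, if enrolment of these patients means their early recruitment, the stability windows could end months before treatment begins. The article does not say which date counts. The subset is 40/120, one third of the patients.

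**Working it through.** **1. Timing.** Data collection starts at month 1 and allocation at month 6. A patient recorded at month 1 waits about 5 months. Counted from the very start of the project, the ceiling is 6. The last patients recruited wait about 0. Adding the 2-month treatment, the interval between recordings runs from about 2 months to at most 7–8 months.

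**2. Is the contrast biased?** Recording precedes randomisation, so the lag falls on both arms alike. A simulation with 20 per arm and 20,000 runs, with a true effect of 0.5 SD and an assumed common drift of 0.3 SD, gave:
- between-arm difference in change: about 0.50 at correlations 0.7, 0.5 and 0.3, so unbiased;
- change within the meditation arm: about 0.80, that is 0.50 + 0.30, so the whole drift is absorbed.

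**3. The article's power figure.** For the treatment-by-time interaction, λ = N·m·f²·ε/(1−ρ), with df1 = (m−1)ε and df2 = (N−2)(m−1)ε. Inputs from Analysis: N = 110, m = 3, ε = 0.75, alpha 0.05, η² = 0.01, so f² = 0.01/0.99 (f = 0.1005). The correlation ρ is not stated.
- ρ = 0.5: λ = 5.0, power 0.54
- ρ = 0.75: λ = 10.0, power 0.84
- ρ = 0.755: λ = 10.2, power 0.85

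The stated 0.85 therefore corresponds to ρ of about 0.755.

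**4. The actigraphy comparison.** N = 40 and m = 2. With two occasions ε is 1, so the main model's 0.75 cannot carry over literally. The interaction detectable with power 0.85 needs λ = 80·f²/(1−ρ) = 9.46:

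| ρ (assumed) | detectable f | η² |
|---|---|---|
| 0.755 | 0.170 | 0.028 |
| 0.70 | 0.188 | 0.034 |
| 0.60 | 0.217 | 0.045 |
| 0.50 | 0.243 | 0.056 |

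All four lie between the conventional small (f = 0.10) and medium (f = 0.25).

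**5. In units of the outcome SD.** Assume 20 per arm (the article gives 60:60 overall and stratifies on this subset). A two-sided t-test at alpha 0.05 with power 0.85 detects 0.972 standard deviations of the change score. The SD of change is √(2(1−ρ)).
- ρ = 0.7: 0.972 × √0.6 = 0.75
- ρ = 0.6: 0.972 × √0.8 = 0.87
- ρ = 0.5: 0.972 × √1.0 = 0.97

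Going from 0.7 to 0.5 raises the variance of change from 0.6 to 1.0. Forty patients then carry the information of 40 × 0.6 = 24. With baseline adjustment (ANCOVA) and the normal approximation, (1.960 + 1.036) × √((1−ρ²)·2/20) gives 0.68 at 0.7 and 0.82 at 0.5, about 20% larger.

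**The case against.** The strongest reply is that nothing here invalidates the planned test, and most of that reply stands.

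- **A reader might infer that the early recording is no baseline at all.** It precedes randomisation, allocation is stratified on the subset, and the planned test is treatment by time against an active control with equal contact time. Drift and regression to the mean enter both arms equally. It is a valid, if distant, baseline.
- **A reader might infer that the power claim fails.** Holding f at 0.170, power drops from 0.85 to 0.71, 0.65 or 0.55 at ρ = 0.65, 0.60 or 0.50. But the article never states f = 0.170. It claims only a small-medium effect, and that description survives even at ρ = 0.5 (f = 0.243). The 0.755 is also back-solved from a model whose occasions run to week 27, so it is not a short-lag correlation.
- **A reader might infer that the whole sleep aim is undermined.** The aim names no instrument, and the sleep questionnaire is completed at T1, T2 and T3. Only the objective measure has the distant baseline.
- **A reader might infer that patients who relapse or change treatment while waiting are randomised anyway.** The article does not say so. It leaves open which date counts as enrolment for these patients.
- **The recording date is implied, not stated,** and the study-procedure figure is not available here. Six months is a ceiling, and how far the lag lowers the correlation is unknown.

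These points limit the size of the concern. They do not remove the gap: no recording near T1 is described, and the change score spans more than the treatment.

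**Conclusion.** The concern holds as a cheap improvement, not as an error that threatens validity. As described, the actigraphic baseline is distant and variably timed (about 0 to at most 5–6 months before treatment) and is not contemporaneous with the T1 sleep questionnaire. Within-arm change therefore cannot be read as the effect of the 8 weeks, and the between-arm comparison may lose precision that it could keep.

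The size of that loss depends on correlations that the article does not give. If the lag takes ρ from 0.7 to 0.5, the detectable difference in change rises by about 0.22 SD (0.75 to 0.97); if it leaves ρ unchanged, nothing is lost. The conclusion assumes that the first recording follows recruitment promptly, as the order of the text implies, and that the subset splits 20:20.

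**What to change.** 1. Keep the early identification of the 40 patients, but record the first two weeks of actigraphy in the weeks immediately before T1 and randomisation, and state that window. The interval between recordings then stays close to the treatment length instead of reaching 7–8 months.
2. If sensors are too few for one date, stagger T1 and allocation of these patients over the opening part of the 11-month intervention phase.
3. Rest the conclusion on objective sleep on the between-arm contrast adjusted for that recording, not on change within the meditation arm.
4. State whether the existing stability windows are counted back from T1 and randomisation for these early-recruited patients, so that they mean the same for all 120.

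**Cost:** scheduling and one eligibility check, with the same sensors and the same number of recordings. The downside is staggered starts and possibly a few patients whose T1 is deferred.

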### Measures

#### Self-report measures

The Multiple Sclerosis Quality of Life*-*54 questionnaire is a multidimensional health-related quality of life measure that combines both generic and MS-specific items in a single instrument [21]. It is composed of 12 subscales along with two summary scores, and two additional single-item measures. The subscales are: physical function, role limitations, physical, role limitations, emotional, pain, emotional well-being, energy, health perceptions, social function, cognitive function, health distress, overall quality of life, and sexual function. The scale has demonstrated good psychometric properties and has been translated into Italian [22]. This assessment will be completed only by patients.

The Medical Outcomes Study Short*-*Form*-*36 health survey will be used to assess caregivers’ quality of life. This is a 36-item scale constructed to survey health status and quality of life [23], that investigates eight health aspects: limitations in physical activities because of health problems; limitations in social activities because of physical or emotional problems; limitations in usual role activities because of physical health problems; bodily pain; general mental health; limitations in usual role activities because of emotional problems; vitality; general health perceptions. It is one of the most widely used instruments for the evaluation of quality of life in many countries in the world, including Italy [24].

The Hospital Anxiety and Depression Scale will be used to assess depression and anxiety levels of all the subjects. This comprises 14 items rated on a four-point Likert scale [25]. It is designed to screen for the presence and severity of depression and anxiety in patients with a physical symptomatology. The scale mainly includes items that are not related to somatic symptoms of depression.

The Langer Mindfulness Scale will be used to assess the level of meditation attunement. This is a 14-item questionnaire that assesses three domains associated with mindful thinking: novelty seeking, engagement, and novelty producing [26]. An individual who seeks novelty perceives each situation as an opportunity to learn something new. An individual who scores high in engagement is likely to notice more details about his or her specific relationship with the environment.

The Medical Outcomes Study sleep measure will be used to investigate the quality of sleep [27]. This measure is composed of ten items, recording on a Likert scale the frequency of occurrence in the previous 4 weeks of symptoms and difficulties typically affecting sleep and daytime activities of patients with chronic illnesses.

Rates of refusal to join the interventions groups after randomization, as well as drop-out rates, will be assessed. The software used will keep an access log, recording the number and duration of accesses, together with a track of used tasks.

The psychological assessment phase will begin with the baseline evaluation, at month 6, with the beginning of the intervention phase. It will last 15 months (6 months after the end of the recruitment phase, to allow follow-up assessments).

